**10.3.3. Expected adverse events**

Expected adverse events that are known to be related to asthma or accompanying viral illness will be recorded on the case report form but not reported. These will include cough, fever, respiratory distress, nausea/vomiting, diarrhea, sore throat, nasal congestion, supplemental oxygen, use of high-flow nasal cannula, skin rash, diaper rash, asthma-related hospitalization, asthma-related unscheduled medical visits with 72 hours of index presentation, IV insertion, sinus tachycardia.

The product monograph mentions the following as magnesium-related potential adverse events: flushing, sweating, hypotension, circulatory collapse, cardiac and central nervous system depression and respiratory depression.

While flushing and sweating will be considered expected and unreported adverse events, the remaining events, while exceedingly unlikely, mandate ICU admission, and would thus be considered SAEs.

Magnesium blocks the neuromuscular transmission and acts as a CNS depressant. Therefore, the theoretical adverse effects with IV Mg may include a transient drop in blood pressure, apnea and heart block. However, only hypotension has been reported with any frequency, which is low.

**10.3.4. Time Period and Frequency for Event Assessment and Follow-Up**

All Adverse Events (AEs) or Serious Adverse Events (SAEs) with start dates occurring any time after receiving the study intervention until 3 days (for non- serious AEs) or 3 days (for SAEs) after the last day of study intervention will be documented.

Participants who are discharged from the ED will receive a survey via email or phone call 72 hours (3 days) after leaving the ED to gather information on any events since leaving the ED.

Participants who are admitted to the hospital for an SAE will be followed for outcome information until resolution or in the opinion of a qualified physician delegate, the participate is stable and does not require further follow-up. These participants will not receive the survey 72 hours (3 days) later.

**10.3.5. Reporting of Adverse Events**

Version Date: June 25, 2025 (v3.0)

Page **32** of **54**

[figure not shown]

**MAGICIAN** Clinical Trial Protocol

All **unexpected adverse events** will be reported to The Hospital for Sick Children Research Ethics Board according to The Hospital for Sick Children’s Adverse Event Reporting requirements and as per the participating site’s local institutional and regulatory requirements.

All serious, unexpected adverse drug reactions to the study medication will be reported to Health Canada within 15 calendar days or for death or life-threatening events, within 7 calendar days. In the latter case, a follow-up report must be filed within 8 calendar days. Adverse reactions will be managed according to the local practices of participating site’s.

**10.3.6. Serious Adverse Event Reporting**

All Serious Adverse Events (SAE) must be reported to [name] within 24 hours of becoming aware of the SAE. The initial report must be emailed to [[contact].](mailto:[contact]) and should contain as much information as available. At a minimum, the report must contain:

•

•

•

•

Name of Site and Principal Investigator, Participant Identification Code, Adverse Event Term,

Study Drug Dose and Start/Stop Dates

[name] will assess the event and confirm if it meets Health Canada’s reporting

requirements.

**Only adverse drug reactions that are both serious and unexpected are subject to expedited reporting to Health Canada**. Expedited reporting of reactions which are serious but expected is not required. Expedited reporting is also inappropriate for serious events from clinical investigations that are considered unrelated to the study product, whether or not the event is expected.

AE will be reported in accordance with site REB and regulatory authorities in accordance with local institutional and regulatory requirements.

Adverse events will be reported to The Hospital for Sick Children through the REDCap database.

[name] will notify all Investigators of all Serious Adverse Events that are reportable to regulatory authorities in Canada from this trial as described above. Investigators must notify their Research Ethics Boards (REBs) according to institutional requirements and file the report and acknowledgement from the REB (e.g. letter from the REB acknowledging receipt, stamp from the REB, signed and dated by REB chair or delegate, acknowledging receipt) with their

Version Date: June 25, 2025 (v3.0)

Page **33** of **54**

[figure not shown]

**MAGICIAN** Clinical Trial Protocol

Investigator Site File.

The Data Safety Monitoring Committee (DSMC) will be notified by email of all unexpected Adverse Events.

**11. SUPPORTING DOCUMENTATION AND OPERATIONAL CONSIDERATIONS**

**11.1.**

**Confidentiality and Privacy**

Participant confidentiality and privacy is strictly held in trust by the participating Investigators, their staff, and the Sponsor(s). This confidentiality is extended to cover the clinical information relating to participants. Therefore, the study protocol, documentation, data, and all other information generated will be held in strict confidence.

Any research information obtained about the patient in this study will be kept confidential. A patient will not be identified by name, only by unique study ID number. The patient’s name or any identifying information will not appear in any reports published as a result of this study. All identifying information will be kept behind 2 security measures or as per equivalent institutional policy, under the supervision of the study/site PI and will not be transferred outside of the hospital.

The study monitor, auditor and other authorized representatives of the Sponsor, representatives of the Research Ethics Board (REB), Governors of the University of Alberta, as represented by the Women & Children’s Health Research Institute, and regulatory agencies may inspect all documents and records required to be maintained by the Investigator, including but not limited to, medical records and pharmacy records for the participants in this study. The clinical study site will permit access to such records.

Study participant research data, which is for purposes of statistical analysis and scientific reporting, will be transmitted to and stored at the Governors of the University of Alberta, as represented by the Women & Children’s Health Research Institute. This will not include the participant’s contact or identifying information. Rather, individual participants and their research data will be identified by a unique study identification number. The study data entry and study management systems used by clinical sites and by Governors of the University of Alberta, as represented by the Women & Children’s Health Research Institute research staff will be secured and password protected. At the end of the study, all study databases will be de-identified and archived at the The Hospital for Sick Children.

**11.2.**

**Safety Oversight - Data Safety and Monitoring Committee (DSMC)**

Safety oversight will be under the direction of the Data Safety and Monitoring Committee (DSMC). The DSMC members will be listed in the DSMC charter.. The members of this committee will not be collaborators of this trial. They will be notified of all serious adverse events and provide feedback to the Trial Steering Committee to determine if the study should be stopped early, continued or terminated. A DSMC

Version Date: June 25, 2025 (v3.0)

Page **34** of **54**

[figure not shown]

**MAGICIAN** Clinical Trial Protocol

charter will be developed in conjunction with the DSMC members to guide the committee process. The DSMC will meet every 6 months or ad hoc if necessary.

**11.3.**

**Participant Safety**

Magnesium has a theoretical potential for hypotension, hypopnea and heart block,45 but only hypotension has been reported in previous studies. The IVMg RCT of 1109 adults reported 8% hypotension46 but nobody had Mg stopped for hypotension.

Pediatric IVMg trials with Mg doses 75 and 100 mg/kg did not report any hypotension (N=101).15,20 While a review of the PECARN Registry found a median dose 50 mg/kg had a hypotension rate of 6.8%,10 the mean decrease in the systolic pressure was 5 mm Hg, with uncertain clinical significance. No hypotension was observed in 3 pediatric pharmacologic ICU studies of 75 mg/kg IV Mg in children

≤30 kg and 50 mg/kg in those >30 kg followed by 40 mg/kg/hour for 4 hours.47-49 Two of our participating sites routinely use 75 mg/kg IVMg. A literature review of pediatric status asthmaticus confirms lack of IVMg toxicity.50 Nonetheless, blood pressure will be measured at 30 and 60 minutes and hourly to 180 minutes. If the systolic pressure drops below the 5th percentile-for-age,51 necessary treatment such as IV fluids will be given. If the hypotension occurs at either the 10 minute or 20 minute measurement, further experimental infusion will be stopped and blood pressure will be treated according to local practices. Hypotension will be defined as systolic blood pressure

<70 mm Hg +(age in years x2) in children 2-10 years old and as <90 mm Hg in those >10 years old. Because the children with unstable airway will be excluded and further inhaled salbutamol will be given if needed, lack of Mg in the placebo group will not endanger these participants. All study patients will be monitored for 180 minutes post-intervention prior to discharge, to ensure safety. Only13/723(1.8%) children discharged post IVMg return to the ED vs 1383/38,623(3.6%) without; IVMg is not associated with re-visits.10

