**DISCONTINUATION AND WITHDRAWAL**

**7.1. Discontinuation of study intervention**

In the exceptional event the patient develops hypotension requiring therapy, apnea, or another adverse event reasonably attributable to Mg and the ED physician feels that the experimental therapy cannot be safely continued, the experimental treatment will be stopped and appropriate treatment given. Hypotension will be defined as systolic blood pressure <70 mm Hg +(age in years x2) in children 2-10 years old and as <90 mm Hg in those

>10 years old.

Lack of clinical improvement/deterioration after experimental therapy will be treated with administration of supplemental oxygen (if needed) and further inhaled salbutamol ± ipratropium treatments. Hypotension after experimental therapy will be treated with supplemental IV fluids/other measures, as per usual clinical practice. Neither of these scenarios apply to discontinuation of study intervention.

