**7.2. Withdrawal from the study**

Participants are free to withdraw from participation of this study at any time upon request. An Investigator may discontinue or withdraw a participant from this study for the following reasons:

•

Withdrawal of informed consent (participant or parent/guardian withdraw for any reason)

•

If the participant’s blood pressure drops below the 5th percentile during the experimental infusion (this needs to be confirmed with manual BP measurement) and the treating physician feels that treatment is required,

Version Date: June 25, 2025 (v3.0)

Page **22** of **54**

[figure not shown]

**MAGICIAN** Clinical Trial Protocol

experimental infusion will be stopped but the child will remain in the study and study allocation will remain blinded. Participants who develop hypotension or receive open-label IVMg during the 180-minute observational period will also remain in the study without unblinding. Participants whose treatment assignment has been unblinded will also remain in the study.

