**9.4. Other rare outcomes**

While the study cannot be powered for their meaningful analysis, we will collect

a) ICU admissions, b) safety outcome of actionable hypotension (systolic blood pressure <5th percentile for age51 treated with IV fluids/other therapy) **(Section 10 Adverse and Serious Adverse Events)**. While many physicians claim to use IVMg to decrease ICU admissions, only 5% (19/372) of hospitalized children received ICU care in MAGNUM.3

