**10.2.**

**Definition of Serious Adverse Events (SAE)**

Version Date: June 25, 2025 (v3.0)

Page **29** of **54**

[figure not shown]

**MAGICIAN** Clinical Trial Protocol

A Serious Adverse Event is any AE that is:

- fatal

•

•

•

•

•

life-threatening

requires or prolongs inpatient hospital stay

results in persistent or significant disability or incapacity a congenital anomaly or birth defect

an important medical event

The term “life-threatening” in the definition of “serious” refers to an AE in which the participant was at risk of death at the time of the event. It does not refer to an AE that hypothetically might have caused death if it were more severe.

Important medical events are those that may not be immediately life threatening but are clearly of major clinical significance. They may jeopardize the participant and may require intervention to prevent one of the other serious outcomes noted above. Examples of such medical events include allergic bronchospasm requiring intensive treatment in an emergency room or at home, blood dyscrasias or convulsions that do not result in inpatient hospitalization, or the development of drug dependency or drug abuse

**Serious Adverse Event (SAE)** will be documented for any incident that consist of:

1. hypotension below the 5th percentile for age requiring medical intervention within 180 minutes of the start of the experimental therapy, or
2. admission to intensive care unit (ICU) at the index ED visit.
3. admission to intensive care unit (ICU) for asthma within 72 hours after being discharged from ED.

These will be reported to the PI, SickKids REB, local REB and the DSMC.

Since hypotension is the only side-effect of IVMg occurring with appreciable frequency, all enrolled patients will be on precautionary frequent blood pressure monitoring as per the study protocol. If the systolic blood pressure drops below 5th percentile for age, treatment will be given as necessary and DSMC will be notified.

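### The protocol gives three conflicting rules for stopping the infusion for hypotension, and two hypotension thresholds with no stated link

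*Protocol*

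**What the plan says.** **Stopping the infusion.**
- Section 11.3: "If the hypotension occurs at either the 10 minute or 20 minute measurement, further experimental infusion will be stopped". No confirmation, need for treatment or physician judgement is attached.
- Section 7.1: the child must have hypotension that needs therapy (or another event attributable to magnesium), and stopping follows when "the ED physician feels that the experimental therapy cannot be safely continued, the experimental treatment will be stopped".
- Section 7.2: the rule applies if systolic pressure "drops below the 5th percentile during the experimental infusion (this needs to be confirmed with manual BP measurement") and the treating physician believes treatment is required. The infusion then stops, and the child stays in the study, still blinded.

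**Threshold.**
- Section 7.1: "Hypotension will be defined as systolic blood pressure <70 mm Hg +(age in years x2) in children 2-10 years old", and below 90 mm Hg above age 10. Sections 6.6 and 11.3 repeat this as the definition.
- Sections 2.3, 7.2, 9.4 and 10.2 use the 5th percentile for age, as does a sentence of 11.3 just before its stopping rule.

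**Outcome and serious adverse event (SAE).**
- Section 9.4, under other rare outcomes, lists the "safety outcome of actionable hypotension (systolic blood pressure <5th percentile for age51 treated with IV fluids/other therapy").
- Section 10.2 counts as an SAE "hypotension below the 5th percentile for age requiring medical intervention within 180 minutes of the start of the experimental therapy".
- Section 10.3.3 lists the adverse events named in the product monograph, hypotension among them. It sets aside flushing and sweating and says "the remaining events, while exceedingly unlikely, mandate ICU admission, and would thus be considered SAEs".

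**Blood pressure schedule.** Section 11.3 lists readings at 30 and 60 minutes and then hourly. Section 2.3 and the schema also include 10 and 20 minutes.

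**The concern.** These are bedside instructions for children during an infusion, at six sites. Section 10.2 calls hypotension the only side effect of magnesium seen with appreciable frequency. If the rule depends on the section consulted, two children with the same reading can be managed differently and both sites can claim compliance.

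Two analysis consequences follow. First, a stopped infusion delivers less drug, and Section 6.2 justifies the dose as protection against a null result from undertreatment. Second, Section 9.5 plans a per-protocol sensitivity analysis, and who completed the infusion bears on membership of that set. In addition, 9.4 and 10.2 judge hypotension by a threshold other than the one that 6.6, 7.1 and 11.3 call the definition.

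**Working it through.** The plan states no figure to reproduce. The check is a comparison of the sections, with arithmetic for scale only.

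**Step 1: the stopping rules.** Take a child who is below both thresholds at the 10-minute reading, so that the choice of threshold plays no part.

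| Situation | 11.3 | 7.1 | 7.2 |
|---|---|---|---|
| Low on the monitor, not confirmed manually | stop | depends on need for therapy and judgement | does not call for a stop |
| Confirmed, treatment not thought necessary | stop | does not call for a stop | does not call for a stop |
| Confirmed, treatment thought necessary, infusion judged safe to continue | stop | does not call for a stop | stop |
| Confirmed, treatment thought necessary, infusion judged unsafe | stop | stop | stop |

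The three sections plainly agree only in the last row. No section is said to prevail.

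**Step 2: the thresholds.** The formula is 70 + 2 × age for ages 2 to 10, and 90 mm Hg above 10:
- age 2: 70 + 4 = 74
- age 5: 70 + 10 = 80
- age 6: 70 + 12 = 82
- age 10: 70 + 20 = 90

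A 6-year-old at 80 mm Hg is therefore hypotensive by the formula. The protocol prints no 5th-percentile values, so whether this child is also below the percentile, and how far apart the two thresholds lie, cannot be worked out from it.

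**Step 3: the SAE wording.** Sections 9.4 and 10.2 match: below the 5th percentile, and treated or needing intervention. Section 10.3.3 makes hypotension an SAE by way of mandated intensive care, with no threshold and no treatment condition. Treated hypotension below the 5th percentile is an SAE either way. Untreated hypotension is an SAE only under 10.3.3. The intensive-care statement also sits badly with 7.1, which has hypotension after the infusion managed with IV fluids or other measures in usual practice.

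**Step 4: dose delivered.** Assuming a constant rate over 30 minutes, stopping at 10 minutes gives 10/30 = one third of the dose, and at 20 minutes 20/30 = two thirds.

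**Step 5: scale.** Inputs are 96 children per group (Section 9.1) and the rates quoted in Section 11.3.
- Registry, median dose 50 mg/kg: 0.068 × 96 = 6.5 children.
- Adult trial: 0.08 × 96 = 7.7 children.
- Paediatric trials at 75 and 100 mg/kg (N = 101): none reported, so 0.

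These are expected counts of all hypotension. Children affected by the conflict are a subset: those whose low reading falls during the infusion and who are in one of the first three rows of the table, or between the two thresholds. The protocol gives no basis for sizing that subset.

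**The case against.** **The formula may be the working version of the percentile.** In 11.3 the percentile, the stopping rule and the formula follow one another, so this reading is natural. The protocol does not say so, however, and 9.4 and 10.2 never mention the formula. Conversely, a reader might take the title of reference 51, which speaks of gaps between percentile-based definitions and life-support guidelines, as proof that the two thresholds here differ. It is not proof: the protocol does not identify its formula with any definition named in that title. What stands is that the link is unstated.

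**The rules could all be satisfied at once.** Sections 7.1 and 7.2 say when to stop, not when to continue, so a site could stop whenever any section calls for it. The protocol does not say this, and at 10 and 20 minutes it would leave the confirmation and judgement conditions with no function.

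**Stronger readings that the documents do not support.**
- That the safety outcome and SAE count simply depend on the section followed. The two sections that define them agree. Variation enters only if a site identifies hypotension by the formula, follows 10.3.3, or treats different children because it stopped different infusions.
- That 6 to 7 magnesium children would be managed or counted differently. That is the expected number with any hypotension at a registry rate, not the number on whom the rules disagree.
- That this matches the 5% non-compliance allowance in 9.1. That allowance is for crossover between arms, and a shortened infusion is not crossover.
- That safety rates by arm would not be comparable across sites. Randomisation is blinded and stratified by site, so differences in local practice fall on both arms.

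**The primary analysis is little affected.** This stands. Section 7.2 keeps these children in the study and 9.5 adopts intention to treat.

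**The schedule in 11.3 is a drafting slip.** Agreed: several other sections include the 10- and 20-minute readings. It still needs correcting, because the 11.3 rule relies on them.

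**Conclusion.** The protocol is wrong as written. Its three stopping rules for the same event give different instructions for a low reading at 10 or 20 minutes, and its two thresholds are not related to each other. Section 10.3.3 adds a third description of hypotension, as an SAE with no threshold or treatment condition. The contradiction rests on the text alone and needs no numerical assumption.

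Its size cannot be computed. If the 6.8% registry rate, observed at a lower median dose, carried over, about 6 to 7 of 96 magnesium children would be expected to have hypotension. The number affected by the conflict would be no larger than that and could be zero. The consequences are for patient safety, dose delivered and the per-protocol set. No effect on the primary intention-to-treat comparison has been shown. No view is taken here on which threshold or stopping rule is clinically right.

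**What to change.** The clinical investigators should:
1. Reconcile Sections 2.3, 6.6, 7.1, 7.2, 9.4, 10.2, 10.3.3 and 11.3 to one definition of hypotension and one stopping rule, both of their choosing.
2. State how the age formula relates to the 5th percentile for age.
3. Use the chosen definition for both the safety outcome in 9.4 and the SAE in 10.2, and align 10.3.3 with it.
4. Correct the 11.3 blood pressure schedule to include the 10- and 20-minute readings that its rule uses.

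Optionally, tabulate by arm the systolic readings below each threshold, treated or not. The readings are already collected, so this adds no measurement.

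The cost is amendment wording and a note to sites. Sample size, visits and the primary analysis do not change.

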**11.4.**

**Study Monitoring**

Monitoring of the trial will be performed to verify that:

- The rights and well-being of participants are protected;

•

The reported trial data are accurate, complete, and verifiable from source documents; and

The conduct of the trial is in compliance with the currently approved protocol/amendment(s), ICH GCP, and local regulations and requirements.

•

The Sponsor will be responsible for all monitoring activities. Any trial-related duty or function transferred to and assumed by a third party, including monitoring and auditing, will be specified in a clinical trial agreement and oversight provided by the Sponsor.

The monitoring plan for the trial will be documented prior to the activation of the study and include the following;

•

Follow risk-based practices,

Version Date: June 25, 2025 (v3.0)

Page **35** of **54**

[figure not shown]

**MAGICIAN** Clinical Trial Protocol

•

•

Document the rationale for the chosen monitoring strategy,

Reference the Sponsor’s process that will be followed to address situations of

non-compliance,

Describe the monitoring responsibilities of all the parties involved, and Outline the data and processes to be monitored.

•

•

The site Investigator(s)/delegate(s) will allow direct access to source data/documents for the purposes of monitoring by the Sponsor, and inspection by regulatory authorities, both domestic and foreign (if applicable). It is important that the Sponsor, site Investigator and site personnel are available during monitoring visits and inspections, and that sufficient time is devoted to the process.

Monitoring procedures will be implemented beginning with the data entry system and data checks that will be run on the database will be generated. Any missing data or data anomalies will be communicated to the site(s) for clarification/resolution.

Monitoring reports will be issued after each monitoring visit for review and follow up by the Sponsor, site Investigator, and appropriate management and personnel responsible for trial and site oversight.

